## **Data collection**

Age, parity, body mass index, smoking history, time since menopause, use of hormone replacement therapy, medical and obstetric history, previous pelvic floor and gynecological surgery will be recorded. All patients will undergo routine pelvic examination, which includes routine bimanual examination, vaginal inspection in a 45°semi-upright position for staging uterovaginal prolapse by POP-Q on maximum Valsalva effort in the lithotomy position. Routine ultrasound examination to exclude uterine or ovarian disease and cervical screening will be performed to exclude high-risk cervical dysplasia. One-hour pad test and occult stress urinary incontinence test and uroflowmetry will be administered to all participants.

Patients will complete four questionnaires. The Chinese version of the pelvic floor impact questionnaire short form (PFIQ-7) and PFDI-20 will be used to measure the impact of prolapse on patient's quality of life before surgery, as well as the degree of postoperative symptom improvement at one year and three year post-operatively [11]. For sexually active women, the Chinese version of the pelvic organ prolapse/urinary incontinence sexual questionnaire short form (PISQ-12) will be administered [12]. The patient global impression of change (PGI-C) inventory will be administered to assess each subject's perception of change of their prolapse condition after surgery using a 7-point Likert scale ranging from "much worse" to "much better".

Perioperative parameters will be documented, including operative time, estimated blood loss, length of hospital stay, postoperative pain score (visual analogue scales, VAS), return to spontaneous voiding time. Peri-operative complications will be recorded and scored according to the Clavien–Dindo classification.

Cost of admission is all the hospitalization expenses including the prescription drugs, laboratory and radiology, surgery and anesthesia fee and material fee, et al.

Patients will visit the hospital at 3 months, 1 year and annually after surgery. A physical examination including POP-Q will be performed and complications will be recorded by member of the research team blinded to the intervention. Mesh related complications such as dyspareunia, pelvic pain and mesh erosion/complications will be categorized using the IUGA/ICS joint terminology CTS coding system. De novo

dyspareunia is defined as those without baseline bothersome symptoms who developed bothersome dyspareunia during the follow up time. De novo stress urinary incontinence is defined as those without baseline bothersome symptoms that developed bothersome stress urinary incontinence symptoms. For patients who do not show up for their post-operative appointments, phone contact will be attempted. If they are contacted but refuse to continue to participate in the study, the reason for dropping out will be assessed.

The enrollment of our study has been completed in October 2019, all the patients had finished operation, and it is the follow-up stage after operation. During the COVID-19 pandemic period, the protocol was adjusted as follows:

1. Under the permission of national and local laws and regulations, patients are encouraged to visit the hospital for follow-up, and the research group should take care of them as much as possible. The safety of patients should be fully considered.
2. The 3-months follow-up after operation could be postponed as appropriate.
3. For patients who have reached the primary end point of 1-year after operation, if they can't visit hospital due to various reasons, they should be followed up by telephone. The survey of questionnaires will be conducted by research staff. When the situation allows, those patients would be encourage to return hospital for physical examination as soon as possible.
4. In case of any problem during the epidemic, each center can report to PI at any time. Quality control will be conducted online. PI will supervise and check the uploaded data irregularly. The mid-term meeting will also be held online.

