### **Hypothesis**

1. The composite outcome of TVM repair using self-cut mesh will be non-inferior to the TVM repair using mesh-kit.
2. TVM repair using self-cut mesh will be non-inferior to the TVM repair using mesh-kit with respect to disease-specific quality of life, sexual function scores and complications.
3. The TVM repair using self-cut mesh will be associated with lower total hospital charges than the TVM repair using mesh-kit.

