### **Study population and recruitment**

Inclusion criteria:

1.Symptomatic POP with apical and/or anterior vaginal prolapse stage III-IV. Only patients with moderate posterior vaginal prolapsed stage I-II ( $C > +1\text{cm}$  or  $Ba > +1\text{cm}$ , with  $Bp \leq +1\text{cm}$  by the POP-Q) will be included. Those with Stage III-IV posterior prolapse will be excluded.

2.Subjects must be more than 3 years after menopause or more than 55 years old, and less than 75 years old.

3.Subject chooses transvaginal mesh treatment after appropriate surgical counselling.

4. Subject is willing and able to comply with the follow-up regimen.

5.Subject is capable of providing informed consent.

Exclusion criteria:

1. High surgical risk due to medical co-morbidities such as, active gynecologic and urinary tract infection, anticoagulation treatment or coagulation disorders, prior pelvic radiation therapy, neurologic or medical condition affecting bladder and bowel function (e.g., multiple sclerosis, spinal cord injury or stroke with residual neurologic deficit), chronic pelvic pain.

2. Need for concomitant anti-incontinence procedure. We want to minimize the interference of other procedures.

Women eligible for this trial will be provided with the information on the objectives, designs, methods, possible advantages and disadvantages of the treatment, and they can refuse or withdraw at any time with no consequences for their treatment. Before randomization, written informed consent will be obtained.

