### **Statistical analysis**

Characteristics of patients and baseline comparisons

Baseline characteristics will be presented by treatment group. Frequency and percentages will be used to describe categorical variables, and means and standard

deviations (SDs) or interquartile range used to describe normally distributed continuous data. We considered the independent sample test or the non-parametric Mann-Whitney test for continuous outcomes, and the  $\chi^2$  test or Fisher's exact test for categorical outcomes.

The following baseline characteristics will be presented:

- Age
- Parity
- body mass index
- smoking history
- time
- since menopause
- use of hormone replacement therapy
- medical and obstetric history,
- previous pelvic floor
- gynecological surgery

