### **Description of analyses**

#### Primary outcome

The primary outcome measure is a composite surgical success variable measured at 1 year after surgery, defined as follows:

1. Absence of vaginal bulge symptoms as indicated by a rating of 0 on question 3 of the Pelvic Floor Distress Inventory-20 (PFDI-20): "Do you usually have a bulge or something falling out that you can see or feel in your vaginal area?"
2. No additional re-treatment (surgical or not) for POP
3. No POP-Q point at or beyond the hymen (i.e., Aa, Ba, C, Ap, Bp all < 0 cm)

All estimated difference with their 95% confidence intervals in primary outcome will be reported, the Agresti-Coull method will be used to calculate 95% CIs for differences in proportions.

We will apply multiple imputation techniques (five imputed datasets) for all women with missing data on primary outcome. Robustness of primary outcome will be

evaluated in sensitivity analyses performed in the ITT population without imputation. We will also conduct a secondary analysis of primary outcome based on per-protocol population, which excludes all patients who had a protocol deviation.

The secondary outcomes

- Anatomic outcome (POP-Q score) of each vaginal segment
- Symptomatic improvement-relief of symptoms of pelvic floor disorders, including urinary, bowel and sexual function using validated instruments
- Intraoperative parameters
- Complications
- Costs, defined as the direct total charges for the surgical admission including operation, medication and use of materials (e.g., surgical mesh)

We will consider the independent sample test or the non-parametric Mann-Whitney test for continuous outcomes, and the  $\chi^2$  test or Fisher's exact test for categorical outcomes. We will use paired sample t test to compare mean continuous data within groups. For anatomic outcomes (POP-Q score) and symptomatic improvement outcomes, we will compare the changes from baseline to 1-year follow up.

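### New bothersome stress incontinence is counted without regard to the baseline occult stress test, so unmasked and newly arising leakage are reported as one "de novo" figure and a collected baseline variable goes unused

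*Combined protocol and SAP*

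**What the plan says.** The current protocol, under Data collection, defines the event by symptoms: "De novo stress urinary incontinence is defined as those without baseline bothersome symptoms that developed bothersome stress urinary incontinence symptoms". The sentence follows directly on the coding of mesh-related complications and the matching definition of de novo dyspareunia. The first protocol edition has the same text.

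The pre-operative work-up paragraph of that section says: "One-hour pad test and occult stress urinary incontinence test and uroflowmetry will be administered to all participants". The trial enrols women with "Symptomatic POP with apical and/or anterior vaginal prolapse stage III-IV". The second exclusion criterion is "Need for concomitant anti-incontinence procedure. We want to minimize the interference of other procedures"; it does not mention the test result.

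Hypothesis 2 claims non-inferiority of self-cut mesh "with respect to disease-specific quality of life, sexual function scores and complications", and no margin is given for any of these. The final SAP compares categorical secondary outcomes by the chi-squared "test or Fisher's exact test for categorical outcomes", without stratification. Its list headed "The following baseline characteristics will be presented" does not contain the occult test. Nor do the protocol's Data analysis section, the SAP subgroups or the schedule table.

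**The concern.** In advanced anterior or apical prolapse, the prolapse itself can hide leakage. An occult stress test looks for exactly that. When a test-positive woman without symptoms leaks after repair, the trial's own record shows that the leakage was already present, but the definition calls it de novo.

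Two things are at stake. First, the trial also aims to describe how titanium-coated mesh performs, and a de novo rate that includes unmasked cases overstates new incontinence as a harm of that repair. Second, the test result probably predicts postoperative leakage, so an arm comparison that ignores it gives up some precision. Precision matters here because non-inferiority on complications is claimed with no margin, and an imprecise null result could be taken as support.

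**Working it through.** **What the text allows.** The documents give no rate, margin or power for de novo stress incontinence, so there is no stated figure to reproduce. The logic is as follows:

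1. The definition needs no bothersome symptoms at baseline and bothersome symptoms later. The test plays no part.
2. Exclusion 2 depends on the need for an anti-incontinence procedure. Nothing says that a positive test meets it.
3. A test-positive woman without symptoms can therefore be enrolled and later counted as de novo.

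**Inputs for an illustration.** From the SAP: 142 women per arm. All other inputs are assumptions: test-positive share f = 0.10-0.40; kit-arm leakage po = 0.30-0.50 in test-positive and 0.10 in test-negative women; self-cut leakage 0.20 in test-negative women.

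**Share of kit-arm events that are unmasked.** Kit rate p = f·po + (1−f)·0.10; share = f·po/p.
- f = 0.3, po = 0.4: p = 0.12 + 0.07 = 0.19; share = 0.12/0.19 = 63%.
- Over the whole range: 25% to 77%. The width shows that the overstatement cannot be estimated from the documents.

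**Variance removed by stratifying (kit arm).** 1 − [f·po(1−po) + (1−f)·0.09]/[p(1−p)].
- Example: 1 − (0.072 + 0.063)/0.1539 = 12.3%.
- Range: 3.4% to 20.0%.

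**Power, two-sided 5%.** Power = Φ(d/SE − 1.96), where d is the overall risk difference. Unstratified, SE² = [sum over arms of p(1−p)]/142. Stratified by the test (Mantel-Haenszel risk difference, approximated with stratum shares f and 1−f), SE² = [f × (sum over arms in test-positive women) + (1−f) × (0.09 + 0.16)]/142.

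*No arm effect in test-positive women* (f = 0.3, po = 0.4):
- Rates 0.19 and 0.26, so d = 0.07. This is the 10-point effect diluted by 1−f.
- Unstratified: SE = √[(0.1539 + 0.1924)/142] = 0.0494; power 29%.
- Stratified: SE = √[(0.3 × 0.48 + 0.7 × 0.25)/142] = 0.0474; power about 32%.
- Gain over the whole range: about 1 to 4 points.

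*Same 10-point effect in both groups* (f = 0.3, po = 0.4 rising to 0.5):
- Rates 0.19 and 0.29, so d = 0.10 with no dilution.
- Unstratified: SE = √[(0.1539 + 0.2059)/142] = 0.0503; power 51%.
- Stratified: SE = √[(0.3 × 0.49 + 0.7 × 0.25)/142] = 0.0476; power 56%.
- Gain over the whole range: about 1 to 8 points.

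These figures treat all 142 women per arm as at risk. Women with bothersome symptoms at baseline drop out of the denominator, so actual power would be lower.

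**The case against.** **The definition is a legitimate choice.** Newly bothersome leakage after surgery is a bad outcome for the woman whatever its mechanism, and de novo dyspareunia is defined in the same way. This stands, and it is the reason not to replace the symptom-only count.

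**The arms are balanced.** Allocation is randomized 1:1 and stratified by center, so test-positive women are expected in equal proportions. This also stands: the plan does not tilt the comparison toward either arm.

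**A reader might infer that pooling hides a true arm difference.** The documents do not support that. It requires a smaller arm effect in test-positive women, and no passage speaks to this. With the same absolute effect in both groups, the risk difference is not diluted.

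**A reader might also set power in test-negative women alone against the pooled comparison**: 62% against 50-54% at f = 0.1, or 51% against 27-32% at f = 0.3. That contrast belongs to a restricted analysis and holds only with no arm effect in test-positive women. The stratified overall estimate keeps the same diluted difference and reduces only the variance. With an equal effect in both groups, restriction can lose power (f = 0.3, po = 0.3: 51% restricted, 55% pooled).

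**The plan may handle part of this.** The final SAP allows logistic regression on baseline covariates after an important imbalance. That is conditional and does not name the test. Urinary symptoms are also compared separately on validated instruments. The SAP baseline list omits prolapse stage too, although stage is a subgroup factor, so the absence of the test from that list does not prove that it would go unreported.

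**Few women may be affected.** Sites may have used the test when applying exclusion 2. No passage says so, but none rules it out.

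**Conclusion.** The point holds as a minor one. The definition combines unmasked and newly arising leakage, the test that separates them is planned for everyone, and no analysis text uses it. The de novo rate in each arm is overstated if it is read as new incontinence; the size is unknown. The comparison between arms loses some precision: about 3-20% of the variance, worth roughly 1 to 8 points of power under the assumed rates.

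The conclusion rests on two readings. The test is taken as a baseline measurement because it appears in the work-up paragraph, although the schedule table does not list it. De novo stress incontinence is taken as one of the complications in hypothesis 2 because of where its definition stands; neither SAP itemises complications. The primary outcome is not affected.

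**What to change.** Keep the symptom-only count as the overall measure, so that results remain comparable with reports using that definition. Then:

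- Add the occult stress test result, by arm, to the final SAP's baseline characteristics.
- Report new bothersome stress incontinence separately for test-negative women (de novo) and test-positive women (unmasked), with the arm risk difference and 95% CI in each group.
- In the final SAP's secondary outcomes, make the overall arm comparison a Mantel-Haenszel risk difference with 95% CI, stratified by the baseline test.

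The cost is wording in the SAP and in the definition. The test is already planned for all participants, so no new data are needed and treatment does not change. The drawback is small counts in the test-positive group, so those intervals will be wide. If few women tested positive, the baseline table will show it and nothing is lost.

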### **Intervention**

In each center, all surgeries will be performed by physicians experienced with both surgical methods. In this study, all women with an intact uterus will undergo hysterectomy prior to mesh placement.

### **Modified self-cut mesh procedure**

This surgical procedure will be performed according to the surgical technique that was described previously [5], which can be summarized as follows.

Self-cut mesh procedure: A single piece of polypropylene mesh (TiLOOP®10 cm×15 cm; pfm medical ag, Germany) will be cut into two parts for the anterior and apical compartment reconstructions. The anterior mesh includes four arms and a joint portion and the apical mesh is composed of two rectangular strips. To reconstruct the anterior vaginal wall, a longitudinal incision will be made into the anterior vaginal mucosa starting t 3 to 4 cm cephalad to the urethral meatus and extending up to the vaginal apex. The vesicovaginal space will be dissected with both blunt and sharp separation until the bilateral obturator internus muscles and the arcus tendinous fascia pelvis (ATFP) are palpated at the level of the ischial spines. Using the obturator puncture needle designed and made for the self-cut procedure, the superficial arms of the anterior mesh will be advanced from an incision 1 cm proximal to the prepubic end of the ATFP to the skin incision at level of clitoris. The deep arm is then advanced from the ATFP 3 to 4 cm away from the ischial spine to cutaneous incision 2 cm inferior and 1 cm lateral to the first incision. The four arms of the anterior mesh are drawn from the vaginal to perineum and the mesh is flattened into the vesicovaginal space below the bladder. The middle compartment and the posterior vaginal wall are then addressed. A mucosal incision is made in the midline posterior vagina from the level of the vaginal apex to approximately halfway down the posterior vagina. Sharp and blunt dissection continues laterally until the ischial spines and sacrospinous ligaments can be palpated on both sides. Skin incisions are made 3 cm lateral and 3 cm inferior to the anus on both sides. A needle is used to puncture through the anorectal fossa and then through the sacrospinous fascia and the spine fascia near the ischial spine. Rectangular strips of mesh are drawn from the inside to the outside, and the mesh strips are fixed to bilateral uterosacral ligaments. Tension-free placement is ensured before mesh was trimmed at the skin. We close the vaginal mucosa and skin with absorbable sutures. We use traditional posterior colporrhaphy to repair the distal two thirds of the posterior vaginal wall.

### **Mesh-kit procedure**

This surgical procedure using the commercially available titanium-coated polypropylene mesh with six arms (TiLOOP®Total 6; pfm medical ag, Germany) is

performed as follows. Insertion of the mesh is performed with tunnelers for the transobturator and ischiorectal passage. After colpotomy and preparation of the vesicovaginal fascia, the mesh was implanted according to the manufacturer's advice. The anterior arms inserted through the obturator fascia, the middle arms through the posterior angle of the obturator foramen, and the posterior arms in the sacrospinous ligaments.

After tension-free implantation of the mesh, the colpotomy is closed using a continuous absorbable suture and a vaginal packing is placed until the next morning. Prophylactic antibiotics are administered immediately before the procedure and for 3-4 days after operation according to the surgeon's decision.

### **Statistical analysis**

#### **sample size and power considerations**

The aim of the trial is to test the hypothesis that procedure with self-cut mesh is non-inferior to the procedure with a mesh kit in terms of the composite success rate and safety. According to Fungfeld's report, the anatomic success rate (POP-Q stage  $\geq$  II, different from this proposed study) after 12 months across all compartments was 86% [8]. Based on a success rate of 90% in this study and 10% as the non-inferiority margin (beta 0.2 and one-sided alpha 0.025), 284 patients (142 in each group) would be required. Taking into account 10% who do not continue to the 1-year follow-up visit, a total of 312 patients will be recruited. the procedure with self-cut mesh will be considered non-inferior if the lower limit of the 95% confidence interval in success rates lies above the non-inferiority margin of -10%.

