### **Statistical analysis**

#### **sample size and power considerations**

The aim of the trial is to test the hypothesis that procedure with self-cut mesh is non-inferior to the procedure with a mesh kit in terms of the composite success rate and

safety. According to Fungfeld's report, the anatomic success rate (POP-Q stage  $\geq$  II, different from this proposed study) after 12 months across all compartments was 86% [8]. Based on a success rate of 90% in this study and 10% as the non-inferiority margin (beta 0.2 and one-sided alpha 0.025), 284 patients (142 in each group) would be required. Taking into account 10% who do not continue to the 1-year follow-up visit, a total of 312 patients will be recruited. the procedure with self-cut mesh will be considered non-inferior if the lower limit of the 95% confidence interval in success rates lies above the non-inferiority margin of -10%.

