## **Randomization**

After informed consent is signed, the patients will be registered on the web-based EDC system by a research staff to allocate each a unique study number prior to randomization. Research staff will access the system and, using the study number and initials, request randomization. Patients are randomized in a 1:1 ratio to either "self-cut mesh" group or "mesh-kit" group, according to a computer-generated randomization sequence with a block size of six. Randomization will be stratified according to centers. The patient and surgeon will be informed about the allocated operative procedure after the randomization.

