### **Justification of the sample size**

The aim of the trial is to test the hypothesis that the procedure with self-cut mesh is non-inferior to the procedure with a mesh kit in terms of the composite success rate and safety. According to Fünfgeld et al.'s report, the anatomic success rate (POP-Q stage  $\geq$  II, different from this proposed study) after 12 months across all compartments was 86%. Based on a success rate of 90% in this study and 10% as the non-inferiority margin ( $\beta = 0.2$  and one-sided  $\alpha = 0.025$ ), 284 patients (142 in each group) would be required. Taking into account 10% who do not continue to the 1-year follow-up visit, a total of 316 patients will be recruited. The procedure with self-cut mesh will be considered non-inferior if the lower limit of the 95% confidence interval in success rates lies above the non-inferiority margin of -10%. The enrollment will be more than 10 patients in each center.

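### From the same 284 required patients and 10% loss, the protocol sets recruitment at 312 and the SAP at 316; only 316 fits those inputs, and the effect on power is negligible

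*Combined protocol and SAP*

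**What the plan says.** The sample-size text is nearly the same in four places: the section on sample size and power considerations in the original and the current protocol, and the section Justification of the sample size in the original and the final SAP.

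- **Assumptions (protocol):** "Based on a success rate of 90% in this study", with "10% as the non-inferiority margin" and "beta 0.2 and one-sided alpha 0.025". The SAP states the same values.
- **Allocation (protocol, Randomization):** "Patients are randomized in a 1:1 ratio".
- **Required number (protocol; same figure in the SAP):** "284 patients (142 in each group) would be required".
- **Recruitment target, both protocol editions:** "Taking into account 10% who do not continue to the 1-year follow-up visit, a total of 312 patients will be recruited".
- **Recruitment target, both SAP versions:** "a total of 316 patients will be recruited", attributed to the same 10%.

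No document shows the formula that takes 284 to the recruitment target. The protocol's summary of changes covers only the pandemic adjustments. The SAP's summary of changes lists the minimum number per centre, the handling of missing data and the per-protocol analysis. Neither mentions 312 or 316.

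**The concern.** Two documents that share every input should not reach different recruitment targets. This is a conflict between the current protocol and the final SAP, not between current and superseded text. The original pair shows the same split, so it was never reconciled.

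Two things are at stake. First, a dropout allowance exists to leave the required number after losses, and 312 does not do that at the loss rate the protocol itself states. Second, readers judge whether a trial met its plan against the planned size. A final enrolment of 313, for example, would exceed the protocol's target and miss the SAP's. The ambiguity also carries into the protocol's section on data safety and monitoring, which places an interim analysis at half the sample size: 312/2 = 156 or 316/2 = 158. (The SAP says that no interim analysis is planned, which is a separate conflict.)

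**Working it through.** **Inputs.** From the protocol's sample-size section: success rate 0.90, margin 0.10, one-sided alpha 0.025 (z = 1.960), power 0.80 (z = 0.842), loss 10%. From Randomization: 1:1 allocation. Assumption: the true success rate is 90% in both arms. The text implies this but does not say it.

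**Step 1. Reproduce the required number.** With unpooled variance,

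n per arm = (1.960 + 0.842)² × 2 × 0.90 × 0.10 / 0.10² = 141.28, rounded up to 142; total 284.

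This matches both documents exactly, so the disagreement lies only in the dropout step.

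**Step 2. Inflate for 10% loss.** If a fraction d of those recruited is lost, N recruits leave N(1 − d), so N = 284/(1 − d).

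| Route | Result | Matches |
|---|---|---|
| 284 / 0.90 | 315.6, up to 316 | SAP |
| 142 / 0.90 per arm | 157.8, up to 158; × 2 = 316 | SAP |
| Unrounded 282.56 / 0.90 | 313.96, up to 314 | neither |
| 284 × 1.1 | 312.4, down to 312 | protocol |
| 142 × 1.1 per arm | 156.2, down to 156; × 2 = 312 | protocol |

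None of the division routes gives 312. Multiplying by 1.1 does, but only if the result is rounded down.

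**Step 3. What each target leaves at 10% loss.**

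- 312 × 0.90 = 280.8, which is 3.2 below 284.
- 316 × 0.90 = 284.4, which meets 284.
- The largest loss that 312 can absorb while keeping 284 is (312 − 284)/312 = 28/312 = 9.0%.

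**Step 4. Power.** Power = Φ(0.10/√(0.18/m) − 1.960), where m is the number evaluable per arm and 0.18 = 2 × 0.90 × 0.10.

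| Evaluable total | m | Power |
|---|---|---|
| 280.8 (from 312) | 140.4 | 79.8% |
| 284 (stated requirement) | 142 | 80.2% |
| 284.4 (from 316) | 142.2 | 80.3% |

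The difference between 312 and the stated requirement is 80.2 − 79.8 = 0.4 percentage points. The targets differ by 4 patients, 4/316 = 1.3%.

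**The case against.** **The size is trivial.** Both power figures round to the planned 80%. Part of the shortfall is itself rounding: against the unrounded requirement of 282.56, 280.8 is only 282.56 − 280.8 = 1.8 patients short. This stands in full. A reader might infer that the trial is underpowered or that its conclusion is in doubt because of the dropout step. The figures do not support that.

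**The mechanism is not documented.** A reader might also take it as established that the protocol multiplied by 1.1 where it should have divided by 0.9. No formula is printed, so this is an inference from the arithmetic. One alternative is that 312 was chosen as whole randomization blocks, since 312/6 = 52 exactly and 316 is not a multiple of six. That explanation is weak. The protocol attributes 312 to dropout, and randomization is stratified by centre, so a whole number of blocks overall is not needed. Rounding 316 up to whole blocks would give 318. In any case, the shortfall against 284 does not depend on how 312 was reached.

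**The correct figure is already on record, and missing outcomes are imputed.** Both SAP versions carry 316, and the final SAP applies multiple imputation to women with a missing primary outcome, so the analysis is not confined to completers. This softens the power point, but imputation does not fully restore the information lost. It also leaves the contradiction between the documents untouched.

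**Enrolment is closed.** The current protocol's Data collection section says that enrolment finished in October 2019. This stands and it decides the remedy: changing the number now cannot add patients, and silently replacing 312 would hide which target was actually used.

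**Conclusion.** The point holds as a minor arithmetic and consistency error. Given 284 required and 10% loss, 316 follows and 312 does not. At 10% loss, 312 leaves about 281 evaluable patients and 79.8% power, against 80.2% at 284. The trial has two planned sizes on record, 4 patients apart, with no reconciliation in either summary of changes.

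The power figures assume a true 90% success rate in both arms, the normal approximation with unpooled variance (which reproduces the plan's 284), and an analysis of completers only. The conflict between 312 and 316 depends on none of these. The remedy relies on the statement that enrolment is complete. The Trial status section of the same protocol still gives March 2020 as the expected end of recruitment, and the documents do not report the number actually enrolled.

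**What to change.** Add a dated clarification to both the protocol and the SAP that:

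1. gives one derivation with its formula: 284/(1 − 0.10) = 315.6, so 316 patients, 158 per arm;
2. states which target, 312 or 316, governed recruitment, and how many patients were enrolled;
3. if the governing target was 312, says that at 10% loss it yields about 281 evaluable patients and 79.8% power under the plan's assumptions.

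The 312 should stay visible in the record rather than be overwritten, so that a later reader can see which target applied while recruitment was open.

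The cost is a short note in each document. No further enrolment is needed, and the margin, the alpha level and the analysis do not change.
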